##### The resting-state fMRI scan session (rs-fMRI)

A single-shot T2^*^-weighted gradient echo-planar image (EPI) sequence will be applied (TE/TR/flip angle = 30 ms/2,000 ms/90°, 64 contiguous axial slices with a slice thickness of 3.0 mm).

##### Task-evoked fMRI scan sessions (task-evoked fMRI)

Participants will be instructed to perform two fMRI tasks during the task-evoked fMRI scans. The two fMRI tasks will include n-back working memory task and the RISE task as described above. A single shot T2^*^-weighted gradient EPI sequence will be applied to the two fMRI tasks with the following parameters: TE/TR/flip angle = 30 ms/2,000 ms/90°, and 64 contiguous axial slices will be acquired with a slice thickness of 3.0 mm.

### Secondary outcome assessments

#### Cardiovascular fitness

All participants will be informed to refrain from high-intensity exercise for 8 h and from eating or drinking any beverage for 2 h before the cardiovascular fitness test. Participants will be asked to wear the heart rate (HR) monitor (Polar HR monitor, Mode V800, Finland) to monitor their HR during the entire testing protocol. Cardiovascular fitness will be assessed by the YMCA cycling ergometer test (Golding et al., 1989), which is a widely recommended way to estimate maximal oxygen uptake (i.e., VO_2max_) for adults with Class A risk stratifications (Fletcher et al., 2001). The YMCA cycling ergometer test comprises two to four 3-min consecutive stages on an electronically braked cycle ergometer (Corival IV CPET, Lode, Netherlands) and is targeted to reach the participants' HR according to their 85% age-predicted maximal HRs [HR_max_ = 206 – (0.67 × age_years_) (Gellish et al., 2007)]. Specifically, participants are instructed to pedal at a speed of 50 rpm throughout the test. In the initial stage, participants are asked to cycle at a workload of 150 kgm/min (25 W) for 3 min. The workloads of the following two stages will depend on each participant's HR recorded during the second and third minute of the initial stage (e.g., HR <80 bpm, the workloads for the second and third stages will be 600 kgm and 750 kgm, respectively; HR >100 bpm, the workloads for second and third stages will be 300 kgm and 450 kgm, respectively). The process will be terminated if the participant's HR reaches their 85% age-predicted maximum HR. Finally, VO_2max_ of each participant will be estimated based on the slope of HRs, the workload, and their body weight.

#### Other fitness indices

In addition to cardiovascular fitness, other indices associated with health-related physical fitness (i.e., body composition, muscular fitness, and flexibility) and skill-related physical fitness (i.e., balance and power) will be assessed.

Regarding health-related physical fitness, body composition [e.g., body water, body fat, skeletal muscle mass, body mass index (BMI), and percentage of body fat] will be assessed using a multifrequency, whole body, and segmental body composition analyzer (ACCUNIQ BC380 Body Composition Analysis, SELVAS Healthcare Inc., Daejeon, Korea) with bioelectrical impedance analysis (BIA) technology. Compared to the reference values of dual-energy x-ray absorptiometry, the measuring device demonstrates high correlation coefficients for lean body mass (kg) in Asian men and women (*r* = 0.983 and *r* = 0.957, respectively), as well as high correlation coefficients for percent of body fat in Asian men and women (*r* = 0.881 and 0.893, respectively) (Yang et al., 2018). Each measurement will take around 2 min. Muscular fitness will be assessed using push-ups, and the scores will be recorded as the number of push-ups completed in 30 s. Finally, flexibility will be assessed using the sit-and-reach test, in which participants will be instructed to reach as far as possible with their palms facing down while sitting down on the floor with legs stretched straight out. Further distance indicates better lower back and hip joint flexibility.

As for skill-related physical fitness, participants' balance will be assessed using the Single-Leg Stand (30 s) assessment. Participants will be instructed to perform the test three times with and without their eyes closed. The length of time the participant can maintain their balance will be recorded as the index of balance performance. Finally, the participant's leg power will be assessed using the distance of the Standing Long Jump. The length between the takeoff line and the nearest point of contact on the landing will be recorded as the power performance index.

#### Genotype and blood assays

##### *ApoE* genotype

Blood samples from the antecubital veins will be collected by licensed medical technicians/nurses during participants' first visit to the laboratory before the random assignment. The genotypes will be determined using a polymerase chain reaction method with modification. Two (rs429358: *ApoE* C112R; rs7412: *ApoE* R158C) genes will determine identification of the *ApoE* allele(s) (*ApoE* ε2, *ApoE* ε3, and *ApoE* ε4). Based on the genotypes, participants will be categorized as high risk (*ApoE* ε3/ε4 and *ApoE* ε4/ε4) or low risk (*ApoE* ε2/ε2, *ApoE* ε2/ε3, *ApoE* ε2/ε4, and *ApoE* ε3/ε3) for AD occurrence.

##### Neurotrophic measure BDNF

All participants will be asked to avoid exercising 8 h before the blood test. Following an overnight fast, participants' blood antecubital veins will be drawn by licensed medical technicians/nurses during the Baseline- and Post-Assessments. Approximately, 6 ml of venous blood will be collected by vacutainers (CAT, BD Vacutainer). The blood will then be separated using a centrifuge at 3,000 rpm for 15 min, and the supernatant fluid will be stored at −80°C for serum marker assays. The peripheral serum BDNF levels will be assayed using a ChemiKineTM BDNF Sandwich ELISA Kit (Millipore, Billerica, MA, USA). The procedure has been employed in our previous studies (Chang et al., 2017a).

#### Psychosocial measures

##### Mindfulness

Mindfulness will be assessed by the Chinese version of the Mindful Attention Awareness Scale (CMAAS) (Nien et al., 2020). The CMAAS (Chang et al., 2011) was based on the Mindful Attention Awareness Scale (MAAS) (Brown and Ryan, 2003). The MAAS assesses levels of dispositional mindfulness. The CMAAS is a 15-item questionnaire. Participants respond on a 6-point Likert scale from 1 (almost always) to 6 (almost never). Higher scores are associated with higher dispositional mindfulness. The CMAAS has been shown to have high internal consistency, with Cronbach's alphas at 0.88.

##### Other psychosocial measures

Potential confounding factors associated with psychosocial factors will be assessed using the following questionnaires: sleep *via* a Chinese version of the Pittsburgh Sleep Quality Index (Tsai et al., 2005) and the Chinese version of short forms of the Geriatric Depression Scale (GDS-15) (Sheikh and Yesavage, 1986; Liu et al., 1998), and health-related quality of life *via* the WHOQOL-OLD-Taiwan (Yao et al., 2017).

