## Methods

### Study design and schedule

The multi-domain interventional trial of WE-BFit is designed as a double-arm, randomized controlled trial (RCT) targeting potential factors for promoting working memory, episodic memory, and brain function in cognitively healthy late middle-aged and older adults who are and who are not at genetic risk for AD. The trial is planned to start in April 2022 and aims to recruit 100 eligible participants who will be randomly assigned into two parallel groups (i.e., the multi-domain exercise group, *n* = 50; the control group, *n* = 50). *ApoE* genotypes of eligible participants will be examined at the baseline assessment. Additionally, other primary outcomes (i.e., working memory, episodic memory, and brain function) and secondary outcomes (i.e., multiple components of physical fitness and BDNF) will be assessed before and after the 6-month intervention. This trial will be led primarily by the Faculty of Physical Education and Sport Sciences of the National Taiwan Normal University. A flow chart of the current trial is presented in Figure 2.

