### Statistical analysis

To address whether the 6-month multi-domain exercise program affects working memory or episodic memory performance and brain functioning, we will employ a two-way repeated-measure analysis of variances (ANOVA) of mixed design with group status (i.e., multi-domain exercise group vs. control group) as the between-subject variable and time points (i.e., Baseline-Assessment vs. Post-Assessment) as the within-subject variable, with the Greenhouse–Geisser correction, where deemed appropriate. The two-way ANOVA will be employed individually for each primary outcome. Multiple *t*-test comparisons will be conducted as follow-up by setting the familywise alpha levels at 0.05, prior to a Bonferroni correction.

To address the moderating role of *ApoE* genotype on the effect of the multi-domain exercise program on working memory and episodic memory performance, as well as brain function assessed from neuroimaging metrics, we will employ the three-way repeated-measure ANOVA of mixed design with group status as the between-subject variable, and *ApoE* genotype [i.e., high-risk candidates (*ApoE* ε3/ε4 and *ApoE* ε4/ε4) vs. the low-risk candidates (*ApoE* ε2/ε4, *ApoE* ε2/ε3, *ApoE* ε2/ε2, and *ApoE* ε3/ε3)] and time points as the within-subject variable, with a Greenhouse–Geisser correction where deemed appropriate. In addition, multiple *t*-test comparisons will be conducted as follow-ups by setting the familywise alpha levels at 0.05 prior to a Bonferroni correction.

To address whether the effects of the multi-domain exercise program on working memory, episodic memory, and brain function are mediated by physical fitness and BDNF, we will employ Pearson product-moment correlations to examine relationships between change in physical fitness, BDNF, and the primary and secondary outcomes. Separate mediation analyses will be conducted using PROCESS software for SPSS. Statistical significance of mediators will be considered if the 95% bias-corrected bootstrap confidence interval (5,000 bootstrap samples) does not include zero. For all analyses, age, sex, BMI, and educational levels will be controlled for, and the alpha value will be set at 0.05, prior to statistical adjustment for all analyses.

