Several challenges of this study are worth mentioning. For instance, the current trial will recruit 50 cognitively healthy participants with a genetic risk for AD. Nevertheless, the recruitment of sufficient participants is challenging, given that the prevalence of *ApoE* ε4 allele(s) in Taiwan is only around 20% (Hong et al., 1996; Wang et al., 2011). Unfortunately, this challenge will be further escalated by the occurrence of the COVID-19 pandemic. Although this challenge might be partially alleviated through recruiting *ApoE* ε4 allele(s) carriers from our previous research and the progressive ease of the COVID-19 pandemic in Taiwan, we still expect the inclusion of a sufficient number of participants, especially the *ApoE* ε4 allele(s) carriers, will be difficult. Drop-out and adherence will be other challenges in the current study. Two strategies will be applied to curtail these challenges. First, frequent contacts and regular newsletters will be delivered to all participants from the research group. Furthermore, the multi-domain exercise group can attend two out of 10 optional exercise sessions each week instead of adhering to a fixed exercise schedule. These approaches enhance the personal connection to the study and provide user-friendly access to the exercise program, and we expect this to enhance participants' adherence and minimize the risk of them withdrawing from the intervention (Robiner, 2005). Finally, the current trial collects a considerable amount of outcome measures, and many of them have to be collected in a time-sensitive manner. For instance, to accurately reflect the relationships between physiological conditions and brain health, physical fitness, BDNF levels, cognitive tasks, and fMRI assessments will be completed within 3 weeks before and after the 6-month exercise program, respectively. To overcome this potential challenge, a limited number of participants (e.g., five people) will be grouped as one intervention unit, and the unit will coordinate the most suitable time for initiating the assessments and exercise program.

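### The mediation models omit the sleep, mood and quality-of-life measures collected as potential confounders, so an interval excluding zero supports only an exploratory mediation claim

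*Protocol article*

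**What the plan says.** **Measures.** The section on other psychosocial measures lists the PSQI (sleep), the GDS-15 (depression) and the WHOQOL-OLD (quality of life), introduced with: "Potential confounding factors associated with psychosocial factors will be assessed using the following questionnaires".

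**Covariates.** The Statistical analysis section states: "For all analyses, age, sex, BMI, and educational levels will be controlled for". It gives the three questionnaires no role.

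**Mediation rule.** The same section begins with correlations: "we will employ Pearson product-moment correlations to examine relationships between change in physical fitness, BDNF, and the primary and secondary outcomes". It then runs PROCESS models and sets the criterion: "Statistical significance of mediators will be considered if the 95% bias-corrected bootstrap confidence interval" (5,000 resamples) excludes zero.

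**Timing.** Study design and schedule: "secondary outcomes (i.e., multiple components of physical fitness and BDNF) will be assessed before and after the 6-month intervention". For BDNF, blood is "drawn by licensed medical technicians/nurses during the Baseline- and Post-Assessments". The Discussion confirms the shared windows: "physical fitness, BDNF levels, cognitive tasks, and fMRI assessments will be completed within 3 weeks before and after the 6-month exercise program". During the intervention itself, Table 2 records attendance only.

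**The concern.** An indirect effect is the product of two paths: arm to mediator (a) and mediator to outcome given arm (b). Randomisation makes the first causal but does nothing for the second, because participants are not randomised to their change in BDNF or fitness. Whether b can be interpreted depends on which common causes of the two changes are in the model.

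The protocol identifies candidate common causes and pays to measure them, but the covariate list leaves them out. Someone whose sleep or mood favours both a fitness gain and a memory gain contributes to a mediator-outcome association without any causal path between the two. Mediator change and outcome change also span the same six months, so the data cannot show which moved first.

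At stake is a stated aim of the trial, whether fitness and BDNF mediate the programme's effect. The randomised comparison of the arms is not at stake.

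**Working it through.** **Inputs.** N = 100, split 50/50, and the 95% bias-corrected bootstrap rule come from the protocol. Everything else is assumed, because the protocol gives no figures: the programme's effect on the mediator, a, in SD units; the correlation r of one omitted factor with each change score within arm; and a true mediator-outcome effect of zero. The protocol states no error rate for the mediation rule, so there is no figure of its own to reproduce.

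**Step 1: spurious correlation.** If a factor correlates r with both changes, then within arm the mediator and outcome changes correlate r × r, although neither affects the other:
- r = 0.2 gives 0.04
- r = 0.3 gives 0.09
- r = 0.4 gives 0.16

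**Step 2: hand check of the b path.** With ρ = r² and 100 − 3 = 97 degrees of freedom, the expected test statistic is z = ρ√(97/(1 − ρ²)). Two-sided rejection at 0.05 is P(Z > 1.96 − z) + P(Z < −1.96 − z).
- r = 0.1: z = 0.10, rejection 5%
- r = 0.2: z = 0.39, rejection 7%
- r = 0.3: z = 0.89, rejection 14%
- r = 0.4: z = 1.60, rejection 36%

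**Step 3: the a path.** Its standard error is √(1/50 + 1/50) = 0.2. So a = 0.5 gives z = 2.5 (power about 71%) and a = 0.8 gives z = 4.0 (about 98%). If the programme does not move the mediator, the product is near zero whatever b is.

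**Step 4: simulation of the rule.** Separate Monte Carlo runs used 500 to 600 trials per cell and 300 to 1,000 bias-corrected bootstrap samples (the protocol plans 5,000). Share of trials declaring a mediator when there is none, factor omitted:

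| r with both changes | a = 0.5 SD | a = 0.8 SD |
|---|---|---|
| 0 | 7–9% | 7–9% |
| 0.1 | 8% | 8% |
| 0.2 | 7% | 9% |
| 0.3 | 15–16% | 18–22% |
| 0.4 | 33–36% | 44–45% |

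With 500 trials, the standard error at 16% is √(0.16 × 0.84/500) = 1.6 points. A smaller run (300 trials) gave 12% and 22% at r = 0.3. With a = 0 the rate stayed at or below about 6%, even for r up to 0.6. The 7 to 9% at r = 0 belongs to the bias-corrected bootstrap, not to confounding.

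**Step 5: what adjustment achieves.** Conditioning on the true common factor brings the rate back to about 7 to 11%. That is a best case, because a baseline questionnaire is only a proxy for the factor. Suppose the proxy correlates 0.5 with it (assumed) and r = 0.4. The residual covariance is 0.16 × (1 − 0.25) = 0.12, each residual variance is 1 − 0.16 × 0.25 = 0.96, and the remaining partial correlation is 0.12/0.96 = 0.125. Then z = 0.125 × √(96/(1 − 0.0156)) = 1.23, and b-path rejection falls from 36% to about 23%. The simulated rule moved the same way: 33% to 25% at a = 0.5, and 44% to 32% at a = 0.8.

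**The case against.** Several points on the other side stand.

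- **The inflation is conditional.** It needs an omitted factor correlating about 0.3 or more with both changes, beyond age, sex, BMI and education. The documents give no such figure. Excluding major depression may narrow the GDS-15 range. A stable additive factor cancels in change scores, so only factors related to the amount of change matter.
- **The programme must move the mediator.** That is plausible for fitness. For BDNF, the Background itself says the effect of multi-domain exercise is unknown.
- **The pre/post design is disclosed.** Measuring mediators and outcomes close together is explained in the Discussion. It limits inference but is not an error.
- **The criterion is one of statistical significance.** A reader might infer that the protocol promises a causally established mediator. It does not: BDNF is called a candidate mechanism, and mediation is presented as additional to the primary aim.

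A reader might also infer that the two sections contradict each other outright. They do not. The confounder label is generic, and measuring a possible confounder does not commit the plan to adjusting for it in every model. Nor do the documents support the inference that adding the questionnaires would restore the nominal error rate; Step 5 shows only partial removal.

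One argument does not carry: that covariates are a detail left to an analysis plan. The article fixes a list and applies it to all analyses. The point therefore concerns a stated choice, not a silence.

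**Conclusion.** The concern holds for the mediation analyses. The named covariates leave out measures that the protocol itself calls potential confounders, and the bootstrap rule is applied to a path that randomisation does not protect.

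Under assumed correlations of 0.3 to 0.4 with both changes, and a programme effect on the mediator of 0.5 to 0.8 SD, a non-mediator passes the rule in about 15 to 45% of trials. At 0.2 or below, the rate is hardly distinguishable from what the method gives with no confounding. These correlations and effect sizes are assumptions, so the figures show what could happen and do not predict it.

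Baseline adjustment reduces the problem but does not remove it, and no covariate can supply the missing time order. This is a low-cost improvement to a secondary analysis.

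**What to change.** In the mediation models:

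1. Keep age, sex, education and BMI, and specify BMI at baseline. BMI is also one of the body-composition measures, and its later value may be changed by the programme.
2. Add baseline PSQI and GDS-15, and decide explicitly whether to add baseline WHOQOL-OLD.
3. Add the baseline values of the mediator and of the outcome.
4. Do not enter post-intervention sleep or mood as ordinary covariates. The programme may change them, which would make them parallel mediators or post-randomisation confounders.
5. Amend the claim rule: an interval excluding zero is reported as exploratory and *consistent with mediation*, with a statement that mediator and outcome were measured over the same interval.
6. Add a sensitivity analysis showing how strong an unmeasured mediator-outcome confounder would have to be to bring the indirect effect to zero.

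All the measures are already collected, so the cost is plan wording, one additional analysis, a few degrees of freedom at N = 100 and a more modest claim. The primary group-by-time comparison does not change.

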### Retention and adherence

To maximize participants' adherence throughout the entire study period, participants will be frequently contacted by the investigators or research staff *via* telephone and e-mail. Participants will also be encouraged to contact the research staff or leave messages if they have any inquiries or concerns about the study. Participants will receive financial reimbursement for each of the assessments (~20 US dollars per hour).

### Power analysis

The study will recruit a total sample size of 100 participants for final statistical analyses. The sample size is estimated from an *a priori* power analysis using G^*^Power 3.1.9.4 (power = 0.80, alpha = 0.05) and the effect size (Hedges' *g* = 0.30) based upon our previous meta-analysis that examines the effects of exercise interventions on executive function, including working memory in adults of age 55–65 years (Chen et al., 2020a).

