### Participants

To ensure a sufficient sample size, the sample size calculation for the current study was conducted using G^*^Power version 3.1.9.4 (ANOVA; repeated measures, within-between interaction). Multiple recruitment strategies will be utilized, including online social media advertising and word-of-mouth referrals, as well as posters and flyers placed or distributed in local community centers and organizations. Finally, individuals from previous studies will also be screened for recruiting potential participants. Before participating in the current study, potential participants will be screened by phone, followed by an on-site interview to ensure they meet the inclusion criteria.

Eligible participants (half of them are *ApoE* ε3/ε4 or *ApoE* ε4/ε4 carriers) will be provided sufficient information, and informed consent relating to the study will be provided prior to the initiation of the study. Recruitment, enrollment, and randomization will occur on a rolling basis. Finally, a total of 100 community-dwelling, cognitively healthy adults aged 45–70 years who are able to participate in moderate-intensity exercise will be recruited in a 1-year time period in Taipei, Taiwan. The inclusion and exclusion criteria are detailed in Table 1.

**Table 1 T1:** Inclusion and exclusion criteria for participating in the study.

**Inclusion criteria**	**Exclusion criteria**
- Adults aged from 45 to 70 years	- Diagnosed or self-reported cognitive problems (e.g., mild cognitive impairment or dementia)
- Normal or corrected-to-normal vision	- The diagnosed or self-reported physical disease (e.g., untreated hypertension and chronic heart disease, stroke, brain tumor, musculoskeletal disorders, other exercise contradictions)
- Able to speak and read Chinese	- Diagnosed or self-reported major psychiatric illness (e.g., major depression, schizophrenia)
- Scores of MMSE ≥ 25	- Diagnosed or self-reported neurodegenerative disease (e.g., AD and other dementias, PD and PD-related disorders, Huntington's disease)
- PAR-Q score = 0	- History of severe alcohol or drug abuse
- Able to conduct the exercise with moderate intensity	- History of chemotherapy
- Meet the criteria to undergo MRI	- Unable to complete the MRI scan
	- Traveling consecutively for 3 weeks or more during the study
	- Unwillingness to be randomized to one of the two groups
	- Currently participating in another study trial

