### Randomization and blinding

To minimize the potential bias of individual differences or covariates, eligible participants will be recruited and randomly assigned to either a multi-domain exercise group or an online educational courses control group with a 1:1 allocation ratio using a computerized permuted block randomization algorithm with stratification (Lim and In, 2019). Additionally, the randomization will be stratified by *ApoE* genotype (High-risk: *ApoE* ε3/ε4 and *ApoE* ε4/ε4 vs. Low-risk: *ApoE* ε2/ε2, *ApoE* ε2/ε3, *ApoE* ε2/ε4, and *ApoE* ε3/ε3) to confirm equal allocation to both groups based on these criteria.

The randomization list for the assignment sequence will be created using the IBM SPSS Statistics for Windows (SPSS Inc., Chicago, IL, USA). Except for staff involved in the multi-domain exercise program and online educational program, assessors and data analyzers will be kept blind to participants' group assignments.

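### N = 100 does not give the stated 80% power for g = 0.30 in the group-by-time test unless the baseline-to-post correlation, which is not stated, is about 0.86 or higher

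*Protocol article*

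**What the plan says.** Five statements in the protocol article fix the calculation.

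- Power analysis: "The study will recruit a total sample size of 100 participants for final statistical analyses". The number comes from G*Power with "power = 0.80, alpha = 0.05" and "the effect size (Hedges' *g* = 0.30) based upon our previous meta-analysis".
- Participants: the G*Power option used is given as "ANOVA; repeated measures, within-between interaction".
- Study design and schedule: the arms are "the multi-domain exercise group, *n* = 50; the control group, *n* = 50".
- Statistical analysis: each primary outcome is tested with a mixed ANOVA of two groups by two time points, so the planned test is the one named for the sample size.
- Discussion: "Drop-out and adherence will be other challenges in the current study".

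The article does not give the correlation between baseline and post-intervention values, how g was converted to the effect size that this G*Power option takes, or an allowance for drop-out.

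**The concern.** This G*Power option takes Cohen's f for the interaction, together with a correlation between repeated measures. Hedges' g is a standardised difference between two groups and cannot be entered as it stands. With the test, N, alpha, g and power all stated, the claim can be checked, and over an ordinary range of correlations it fails by a wide margin.

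This is the article's only justification of the sample size. A reader told that the trial has 80% power for g = 0.30 could take a non-significant result as fairly strong evidence against an effect of that size. If power is well below 80%, that inference is not available.

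**Working it through.** **Inputs from the article.** N = 100, 50 per arm; two groups; two time points; alpha 0.05; g = 0.30; target power 0.80; within-between interaction.

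**Input not in the article.** The baseline-to-post correlation, rho. I assume 0.5 to 0.8 and also show values outside that range.

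**Formula.** Noncentral F with 1 and N − 2 degrees of freedom and noncentrality lambda = N × m × f² / (1 − rho), with m = 2 measurements.

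**Step 1: try to reproduce N = 100.** No entry gives N = 100 at 80% power from the stated inputs alone.

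| Entry | N for 80% | Power at N = 100 |
|---|---|---|
| f = g/2 = 0.15, rho = 0.5 | 90 | 0.844 |
| f = 0.15, rho = 0.44 | 100 | 0.801 |
| f = g = 0.30, noncentrality taken as f² × N | 90 | 0.844 |
| f = g = 0.30, rho = 0.5 | 24 | 1.00 |

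The first and third rows are the same calculation: 2 × 0.15² / 0.5 = 0.09 and 0.30² = 0.09, so lambda = 0.09N in both. Both need an unstated step, such as 90/0.9 = 100, to arrive at 100.

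**Step 2: convert g correctly.** In a two-by-two design with a difference in change of g outcome SDs, the interaction term in each cell is ± g/4. So f = 0.30/4 = 0.075. Read the other way, f = 0.15 is a difference in change of 4 × 0.15 = 0.60 SD, twice the cited effect. The f = 0.30 entry with lambda = f² × N is also twice the cited effect, in units of the SD of change: lambda = N × d²/4 = 0.09N gives d = 0.60.

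**Step 3: power with f = 0.075.** At N = 100, lambda = 100 × 2 × 0.005625 / (1 − rho) = 1.125 / (1 − rho), which is 2.25, 3.75 and 5.625 at rho 0.5, 0.7 and 0.8.

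| rho (assumed) | Power, N = 100 | N for 80% | Power, 90 analysed |
|---|---|---|---|
| 0 | 0.18 | 700 | 0.17 |
| 0.3 | 0.24 | 492 | 0.22 |
| 0.5 | 0.32 | 352 | 0.29 |
| 0.6 | 0.38 | 282 | 0.35 |
| 0.7 | 0.48 | 212 | 0.44 |
| 0.8 | 0.65 | 142 | 0.61 |
| 0.85 | 0.77 | 108 | 0.73 |
| 0.9 | 0.91 | 72 | 0.88 |

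**Step 4: cross-check.** The interaction test is a two-sample t-test on change scores, whose SD is sqrt(2(1 − rho)) outcome SDs. At rho = 0.5 that SD is 1, and the noncentrality is 0.30 / sqrt(2/50) = 1.5, whose square is the 2.25 above. A simulation of 40,000 trials gave 0.314 at rho 0.5 and 0.650 at rho 0.8.

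**Step 5: correlation needed and effect detectable.** With 50 per arm, 80% power needs a difference of 0.566 SD of change. Setting 0.30 / sqrt(2(1 − rho)) = 0.566 gives rho = 1 − (0.30/0.566)²/2 = 0.86. The detectable g is 0.566 × sqrt(2(1 − rho)): 0.57 at rho 0.5, 0.44 at 0.7 and 0.36 at 0.8.

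**Step 6: the other reading of g.** If g is standardised by the SD of change, rho drops out. Power is that of a two-sample t-test with d = 0.30 and 50 per arm, about 0.32.

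**The case against.** **Rho is my assumption.** This stands, and it limits the claim. A reader might infer that the trial's actual power is 32% to 65%. The article does not support that as a fact: the range follows from rho 0.5 to 0.8, and at rho 0.9 power would be 0.91. What the article does support is that 80% is not reached below about 0.86. A correlation at or above that value in the full protocol would rescue the outcome-SD reading, but not the change-SD reading.

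**The scale of g cannot be checked.** The cited meta-analysis is not at hand, so whether g is in outcome-SD or change-SD units is open. Both readings are shown above.

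**A journal article condenses.** Leaving out rho or a drop-out rate is not in itself an error. The point is that the stated power, effect size, N and test do not agree with one another at ordinary correlations.

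**The 100 may already include attrition.** 90/0.9 = 100 fits, and the article describes retention measures, so a reader should not conclude that no allowance was made. But none is stated, and the Power analysis section describes the 100 as the number for the final analyses. Even if the allowance was made, the 90 beneath it rests on an f that is too large.

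**Another analysis might recover the power.** Over rho 0.5 to 0.8, baseline-adjusted ANCOVA gives about 41% to 71% and one-sided testing about 44% to 77%. Both fall short, and neither is the planned test. The planned adjustment for age, sex, BMI and education may shift power somewhat; the article gives nothing to quantify that.

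**Conclusion.** The stated 80% power for g = 0.30 is not supported. It needs rho of about 0.86 or more with g in outcome-SD units, and is not reached at any rho with g in change-SD units. Short of such a correlation, an N near 100 appears only when the f entered overstates the cited effect. Which entry was used is not stated, so f = g/2 is a possible source and not an established one.

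A reader might also infer that a true effect of g = 0.30 would be missed more often than found. That does not hold throughout: power passes 0.50 at rho of about 0.715 and is 0.65 at rho 0.8. Nor does the point extend to the other outcomes or to ApoE moderation, since the Power analysis section makes no separate power claim for them.

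Drop-out can only lower these figures. The conclusion assumes equal arms, equal expected baselines, equal variances at the two time points and a two-sided 5% test.

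**What to change.** Keep N = 100 and rewrite the Power analysis section to give:

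1. the scale on which g = 0.30 is defined, and the conversion to f (g/4 if it is in outcome-SD units);
2. the assumed baseline-to-post correlation and its basis, with a range if it is uncertain;
3. the expected attrition, and whether 100 is the number recruited or the number analysed;
4. either the resulting power for g = 0.30 or the effect detectable with 80% power. Before attrition the latter is about g = 0.57, 0.44 or 0.36 at rho 0.5, 0.7 or 0.8.

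The cost is a reworded paragraph and, unless a correlation of about 0.86 or more can be justified, a less favourable stated figure. No participants are added, and the design and the test do not change.
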